#### fNIRS data

An initial band pass filter will be applied to the raw fNIRS data before further processing to remove noise and drifts. Neuroactivity in various regions of interest including, prefrontal, pre-motor, supplementary, and primary cortex, will be analyzed by constructing a general linear model for each subject then estimating parameters and obtaining contrast values of the total oxy-Hb and deoxy-Hb signals. The contrast value images can be averaged within groups and a group analysis can be done using a *t* test. The averaged signal levels of each group will be plotted on a time vs total blood flow graph and compared to determine intervention effect.

### Interim analyses {21b}

Not applicable to study, data analysis is not anticipated until the end of studies (follow-up) for all participants.

### Methods for additional analyses (e.g., subgroup analyses) {20b}

Further statistical analysis may be explored to account for interacting factors including gender, age, and different stages of PD as determined by the Hoehn and Yahr scale.

### Methods in analysis to handle protocol non-adherence and any statistical methods to handle missing data {20c}

Missing data and any data collected not adhering to the protocols will be removed from data analysis.

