### Eligibility criteria {10}

Potential participants will be recruited from the Neurology Department of the First Affiliated Hospital of Dalian Medical University in China. Only individuals who meet the inclusion criteria will be invited to participate in the study.

There will be two populations participating in this study: one will be patients diagnosed with PD with intervention and the other without. A group of healthy participants will be recruited to serve as healthy controls (HC) that will provide the baseline assessment data to gage the severity of PDs in the patient populations.

The following are the inclusion criteria for participants with PD recruitment:
Aged 40–80 years old, both genders, and right-handed;Clinical diagnosis of idiopathic PD according to the 2015 Movement Disorder Society (MDS) Clinical Diagnostic Criteria for Parkinson’s Disease;Rated as stage I to II on the Hoehn and Yahr scale;Score greater than 21 points on the Montreal Cognitive Assessment (MoCA);Maintain a stable dosing of anti-PD or deep-brain stimulation (DBS) treatment throughout the duration of the study;Able to travel to and participate in the data collection process.

Exclusion criteria for participants with PD recruitments include:
Individuals who do not meet the inclusion criteria;Presence of significant hearing impairments;Extensive previous musical training;A history of any other neurological condition (i.e., Alzheimer’s disease, epilepsy, stroke) or psychiatric disorders (i.e., major depression, psychoses).

The HC group will consist of subjects recruited from hospital staff and students as well as students and faculty members from Dalian University of Technology. In addition, participants’ spouses will also be invited to participate. The HC group must have the following qualities to be included:
Aged 40–80 years older, both genders, and right-handed.

HC will be excluded along the same criteria that was established for the PD recruitment.

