## Interventions

### Explanation for the choice of comparators {6b}

The PD intervention group is compared with the PD control group and a healthy control (HC) group. The PD control group is composed of participants diagnosed with PD and who meet the inclusion criteria. This PD control group is instructed to maintain the participants’ prescribed medication and care documented at the time of baseline assessment including any form of deep brain stimulation, if applicable. Any deviation from what was recorded at the time of taking baseline assessments are recorded during assessments and included when analyzing the data.

The second control group, the HCs, is composed of participants who meet the HC group inclusion criteria. This group predominantly consists of healthy spouses of the PD participants and individuals who share similar demographics to the participants diagnosed with PD. Measurements from the HCs are necessary because they serve as a normal, non-pathological benchmark, which has not been recorded before with this specific demographic and type of study paradigm. Furthermore, since spouses typically have similar lifestyles as their partners the measurements taken may help reduce the uncontrollable deviations due to dietary habits, living conditions, and environmental factors. HCs are asked to continue normal routine and must report any major deviations from baseline assessment routine (e.g., new medication to treat non-neurological illnesses that may affect motor movement or major injuries like head trauma). These deviations are noted for data analysis.

The neuronal activities of generating motor movement or processing a rhythmic external cue each should separately elicit measurable neuronal activation. However, when combined, a sensorimotor integration effect occurs such that motor movement is the result of a rhythmic external cue. Thus, the use of the HC and PD controls is to examine how movement coupled with an external sensory cue (a rhythmic auditory stimulus and in this study, music with rich rhythmic contents) impacts motor synchronization and control in PD.

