### Criteria for discontinuing or modifying allocated interventions {11b}

Participants may stop participation at any time during weeks 0–12 due to various reasons including failure to meet inclusion criteria or inability to continue at-home intervention.

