### Sample size {14}

For this study, a total 210 participants (70 participants in three groups with a 10% attrition rate), are recruited over an 18-month period. We aim to recruit an even distribution of age, PD staged I, and II as determined by the Hoehn and Yahr scale, and gender to maximize statistical significance. This study is an exploratory prospective randomized controlled study with the primary outcome being the HbO_2_ value measured by fNIRS. Because there are no pilot study nor previous studies identical to this, the sample size was calculated by using power calculations (where *α* = 0.05, *β* = 80%, and we assume a conservative average difference between the PD groups). Klempir et al.’s study was used to estimate the baseline averages of HbO_2_ changes; however, there are notable inherent differences between this protocol and the referenced study. Klempir et al. describes HbO_2_ changes between participants with and without DBS during a finger tapping exercise [34]. Although our study may involve participants who use DBS as a treatment, we are not examining how various forms of treatment (pharmaceutical or DBS) affect motor control. Thus, the estimated HbO_2_ baselines when DBS is ON from Klempir’s study were approximations of the PD control group’s performance.

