### Plans for communicating important protocol amendments to relevant parties (e.g., trial participants, ethical committees) {25}

Protocol amendments are first discussed with the Steering Committee during organized meeting times and agreed upon prior to formal release to the Ethical Committee and Scientific Research Department of the hospital. Once approval is obtained, a formal document summarizing the necessary protocol amendments are shared with relevant parties, especially trial participants via phone call and mail, with digital copies available upon request. Necessary updates to the clinical trial application are made by the Trial Manager upon approval from the Steering Committee, Scientific Research Department and the Ethics Committee. Should there be any deviations in the protocol, a protocol breach report will be completed and reported to the Trial Manager within 24 h. Data collected will be marked and considered during data analysis.

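### Removing missing and non-adherent data after randomisation turns the comparison of the two PD arms into a complete-case, per-protocol one, with no threshold, no unit of removal and no as-randomised analysis

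*Protocol article*

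**What the plan says.** The section on non-adherence and missing data {20c} consists of one sentence: "Missing data and any data collected not adhering to the protocols will be removed from data analysis". The statistical methods {20a} begin analysis once retained participants have finished week 12 and name two-sample t tests. No section describes an analysis of all randomised participants as assigned.

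Other sections treat the same data differently:

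- Choice of comparators {6b}, on the PD control arm's medication and care: "Any deviation from what was recorded at the time of taking baseline assessments are recorded during assessments and included when analyzing the data".
- Protocol amendments {25}, on protocol breaches: "Data collected will be marked and considered during data analysis".
- Consent provisions {26b}: participants are asked whether their data may be used if they withdraw.
- Discontinuation {11b}: participants may stop at any time in weeks 0–12 "due to various reasons including failure to meet inclusion criteria or inability to continue at-home intervention".
- Eligibility {10} includes a condition that runs past baseline: "Maintain a stable dosing of anti-PD or deep-brain stimulation (DBS) treatment throughout the duration of the study". Concomitant care {11d} repeats it for all participants to whom it applies.

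On what can count as non-adherence, the intervention arm practises 25 minutes a day for 8 weeks on video {11a}. Its videos are scored for adherence and, separately, for accuracy {11c}. The control arm's videos receive one binary adherence score {11c}.

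**The concern.** Randomisation protects the comparison only while the groups analysed are the groups randomised. A rule that drops data for what happened after allocation replaces them with those who complied and were measured. The two arms are asked to comply with different things, so the people left in each need not be comparable.

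The scope for removal is unequal, though not confined to one arm. The intervention arm has 8 × 7 = 56 daily sessions to miss or perform poorly, and two scores. The PD control arm has one binary score, and the stable-treatment condition applies to both. If those who keep up daily tapping are the ones who do better anyway, removing the rest flatters the intervention on tapping, UPDRS and MoCA. Such an error lies outside the stated 5% level and is not reduced by recruiting more people.

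The rule is also not reproducible. With no threshold or unit of removal, and with {6b} pointing the other way, two analysts could follow the article and analyse different populations.

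**Working it through.** **1. The plan's own figure.** Sample size {14} gives "a total 210 participants (70 participants in three groups with a 10% attrition rate"), α = 0.05 and 80% (printed as β, read here as power). It gives no difference or SD, only that "we assume a conservative average difference between the PD groups". The figure therefore cannot be derived from stated inputs. Back-solving with an assumed standardised difference d = 0.5, two-sided:

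n = 2(1.960 + 0.842)² / 0.5² = 62.8, so 63 per arm; 63 / 0.9 = 70; 3 × 70 = 210.

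The d of 0.5 is an assumption that fits; the document does not state it. The allowance is 10% for attrition (70 × 0.9 = 63), described under Recruitment {15} as withdrawal, illness and other uncontrolled factors, with nothing separate for removing non-adherent data.

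**2. The sections side by side.** {20c} removes non-adherent data. {6b} includes deviations from baseline care when analysing the data, and a change of care is also a departure from {11d}. The same record is therefore covered by two opposite instructions. {25} is weaker: marking and considering data does not rule out considering it for removal.

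**3. Size of a possible bias.** All inputs here except the 63 are assumptions. Suppose there is no true effect, 63 participants per arm, and the fraction f with the lowest latent adherence is removed as whole participants. Adherence has correlation r with outcome (higher = better).

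- λ(f) = φ(z_f) / (1 − f), giving λ(0.1) = 0.195, λ(0.2) = 0.350, λ(0.3) = 0.497.
- Bias b = r[λ(f_I) − λ(f_C)], in SD units.
- Variance in a filtered arm: v = 1 − r²λ(λ − z_f).
- SE = √(v_I/n_I + v_C/n_C).
- Two-sided type I error = Φ(−1.96 − b/SE) + 1 − Φ(1.96 − b/SE).

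Example, 20% removed from the intervention arm only, r = 0.3: b = 0.3 × 0.350 = 0.105. v_I = 1 − 0.09 × 0.350 × (0.350 + 0.842) = 0.962. SE = √(0.962/50.4 + 1/63) = 0.187. b/SE = 0.56, and type I error is 8.7%.

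| r | Removed, intervention vs control | Bias (SD) | Type I error |
|---|---|---|---|
| 0 | any | 0 | 5.0% |
| 0.3 | 20% vs 20%, same mechanism | 0 | 5.0% |
| 0.3 | 30% vs 10% | 0.091 | about 7.5% |
| 0.3 | 20% vs 0% | 0.105 | 8.7% |
| 0.3 | 30% vs 0% | 0.149 | 12.0% |
| 0.5 | 30% vs 0% | 0.248 | 26.0% |
| −0.3 | 20% vs 0% | −0.105 | 8.7% |

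**4. Power.** Removing 20–30% of 63 leaves about 50 or 44 in the intervention arm. If d = 0.5 (assumed), the two-sided t test with noncentrality 0.5/√(1/63 + 1/n_I) has power of about 80% with 63, 74% with 50 and 71% with 44.

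**The case against.** **The control arm can be filtered too.** This stands. Its videos are scored for adherence and stable treatment is required of both PD arms. A reader might infer that only the intervention arm can lose data; the document does not support that. It supports unequal exposure.

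**The direction is not established.** This also stands. A reader might infer that the bias must favour the intervention. That needs adherers to have better outcomes, and at r = −0.3 the sign reverses. It is plausible for tapping, UPDRS and MoCA. For HbO2, which {14} names as the primary outcome, nothing in the document fixes the sign.

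**Removal of participants whose MoCA falls is an inference.** MoCA above 21 is an entry criterion, MoCA is also a listed primary outcome, and {11b} mentions failing inclusion criteria during weeks 0–12. A reader might infer that decliners are taken out. No section re-applies the criterion at weeks 4, 8 or 12, and it would act on both PD arms. What remains is that the wording is loose enough to let people leave on criteria judged after baseline.

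**The magnitudes are assumed.** They are. The removal fractions, the correlation, the whole-participant unit and the 0.5 SD are not in the article, and the range properly starts at 5%.

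**An analysis plan may settle this, and the trial is exploratory.** {20c} is a stated rule, which an analysis plan would have to contradict in order to repair. The exploratory label tempers the consequences but does not make a post-randomisation exclusion a randomised comparison.

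**Conclusion.** The rule in {20c} is wrong as written. Followed literally, it replaces the randomised comparison of the PD arms with an undefined complete-case, per-protocol one, and it conflicts with {6b} and sits uneasily with {25}. That conclusion rests on the text alone and is firm.

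The size and direction are not firm. Under the stated assumptions, type I error runs from 5% (equal removal by the same mechanism, or removal unrelated to outcome), through about 7.5% (30% vs 10%, r = 0.3) and 9–12% (20–30% from the intervention arm only, r = 0.3), to about 26% (30% from the intervention arm only, r = 0.5). If the design difference is 0.5 SD, power falls from 80% to about 71–74%. A bias towards benefit is plausible for tapping, UPDRS and MoCA and undetermined for HbO2.

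**What to change.** Replace the sentence in {20c} along these lines: the primary analysis includes all randomised PD participants in the arm assigned, with all outcome data collected, regardless of adherence or treatment change. Missing visits are handled by a method that uses every observed visit (for example, a likelihood-based repeated-measures model), with a sensitivity analysis for the missing-data assumption.

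Keep the adherence-restricted analysis as supplementary, with the score, threshold and unit of removal set in advance. Judge eligibility for the analysis at baseline. Continue the already scheduled week 4, 8 and 12 assessments for consenting participants who stop practising. Reconcile {6b}, {11b}, {20c} and {25}.

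This is mainly wording and adds no scheduled visits. The costs are some dilution of the estimate by non-adherence and modest effort to retain people who have stopped practising. It should be settled before any outcome data are seen.

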### Plans to give access to the full protocol, participant level-data and statistical code {31c}

The datasets analyzed during the current study are available from the corresponding author on reasonable request.

## Oversight and monitoring

### Composition of the coordinating center and trial steering committee {5d}

The roles of the principal investigators (FC, WT, BZ, and ZL), research physicians (LP), and associated researchers ([name], JL) are to advise and agree upon protocols, organize steering committee meetings every other month, lead publications of study reports, and report updates to sponsors and key personnel of the Scientific Research Department of the hospital. The Steering Committee, chaired by ZL, is responsible for agreeing on the final protocol, recruiting and screening of participants, and reviewing the progress of the study to advise changes to the protocol and ensure smooth running of the study. The Trial Manager, LP, is responsible for the trial’s master file, obtaining approval from the Ethics Committee, coordinating audits with the Ethics Committee every quarter, managing enrollment and allocation, releasing official changes of clinical trial protocol to relevant entities and trial participants, scheduling participant assessments, reporting any serious unexpected adverse events, and addressing any questions participants have.

### Composition of the data monitoring committee, its role and reporting structure {21a}

The data collected is predominantly electronic and should be uploaded or manually inputted into the cloud-based storage server via a web interface. The hospital’s Ethics Committee and the study’s Steering Committee have determined that the intervention is considered “low-risk”; therefore, there is no formal data monitoring committee. Instead, the data is be managed by a designated Data Manager, LP, who oversees data recording, provides training to research assistants, and addresses any issues that arise from the cloud storage, data collection, data management, and data access. LP will frequently check and assess that data is collected accurately and reliably. Research assistants report to LP for additional assistance and guidance with the trial’s associated technologies, should issues arise. Any serious unexpected adverse events are expected to be reported to the data manager and thusly to the Steering Committee within 24 h.

### Adverse event reporting and harms {22}

The ETG-4000 fNIRS system has minimal risk. The audio is adjusted to a comfortable level prior to assessment. Consequently, no adverse event reporting plans are applicable to this study. Should an unforeseen serious adverse event occur, a case report is written, and the Trial Manager is notified within 24 h. The case report is expected to be shared with the Steering Committee, Ethic Committee, and trial participants within the next 48 h.

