### Intervention description {11a}

After the baseline measurements, participants in the intervention arm will be trained to do a rhythmic auditory synchronous finger tapping (SFT) intervention task at the hospital and asked to practice at home for a total of 25 min split between two 10-min sets with a 5-min break between the sets every day for 8 weeks. During training sessions participants must listen to the instrumental of a pre-selected well-known Chinese melody, i.e., 荷塘月色 (pinyin: “hé táng yuè sè”; English: “Moonlight over the Lotus Pond” by Phoenix Legend) whose melody duration is 259 s. This song was selected for its strong beat and familiarity to most of the participants. Participants must follow the beats of the melody and tap their right index finger simultaneously to the beats. The training session will be conducted once daily after patients have taken their medication. They are also instructed to take a video recording of themselves with their smartphones for the entire duration of the training. They may also solicit the help of their primary caregivers for the recording. This is for the purpose of monitoring protocol compliance.

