### Outcomes {12}

The primary outcome measurements of this study are the following:
Improvement or preservation of SFT and continuous finger tapping (CFT) performances from baseline measurements for intervention group.Preserved or improved the Unified Parkinson’s Disease Rating Scale (UPDRS) scores from baselines measurements for intervention group in comparison to control arm.Reduced HbO_2_ levels in prefrontal cortex from baseline measurements for intervention group. Preserved or improved n-back task scores from baseline measurements for intervention group in comparison to control arm.Preserved or improved Montreal Cognitive Assessment (MoCA) scores from baseline measurements for intervention group in comparison to control arm.

Secondary outcome measurements of the study include:
Preserved motor control performances, UPDRS scores, HbO_2_ levels, n-back task scores and MoCA scores from baseline measurements in healthy control group.Preserved or aggravated motor control performances, UPDRS scores, HbO_2_ levels, n-back task scores, and MoCA scores from baseline measurements in PD control group.

These outcomes are determined by analyzing the differences between participants’ pre-, 4-week (during), 8-week (post), and 12-week (retention), neuroimaging, neurophysiological, and SFT performance scores as well as compared with the data from the control arms. Individual and grouped averaged measurements are examined.

Music-based therapies often report beneficial and positive results; however, little is known about how music improves neuronal activity and connectivity in individuals with neurological disease. The primary outcome measurements of this protocol: SFT and CFT performances, HbO2, UPDRS scores, n-back, and MoCA scores act as assessments to quantify the effects of a music-based synchronous finger tapping training in individuals with PD. The trial’s outcomes may be used to enhance current clinical care of patients with PD by supplementing or augmenting current PD treatments with music-based exercises. There are currently no anticipated harmful outcomes because the use of fNIRS has been shown to be clinically safe and feasible. Consequently, this study was determined to be a low-risk intervention by the participating hospital’s Ethics Committee and the Steering Committee.

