### Dissemination plans {31a}

Trial results are planned to be predominantly communicated via conferences and manuscript publication in relevant PD and fNIRS related organizations. A formal summary of the study’s results is provided to sponsors who will then produce a publicize copy and manage the dissemination at that time. The attending physicians at the hospital’s PD ward will receive the study’s details, findings, and directions on implementation if they wish to utilize it with their patients. Data sharing arrangements can be made upon reasonable request.

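### The harms section waives adverse event reporting because the equipment is safe, so non-serious harms of eight weeks of daily home tapping are not planned to be collected or compared between the PD arms

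*Protocol article*

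**What the plan says.** All references are to the protocol article.

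- **Adverse event reporting and harms {22}** gives two premises, "The ETG-4000 fNIRS system has minimal risk" and "The audio is adjusted to a comfortable level prior to assessment", and concludes: "Consequently, no adverse event reporting plans are applicable to this study".
- The same section then sets a procedure for serious events: "Should an unforeseen serious adverse event occur, a case report is written, and the Trial Manager is notified within 24 h" and "The case report is expected to be shared with the Steering Committee, Ethic Committee, and trial participants within the next 48 h".
- **Outcomes {12}** reasons in the same way: "There are currently no anticipated harmful outcomes because the use of fNIRS has been shown to be clinically safe and feasible". It then reports that the Ethics and Steering Committees rated the study as a low-risk intervention. Provisions for post-trial care {30} also expects no harm because of the equipment.
- **Intervention description {11a}** defines the randomised treatment as tapping the right index finger to a melody at home, "split between two 10-min sets with a 5-min break between the sets every day for 8 weeks".
- **Composition of the data monitoring committee {21a}** uses the low-risk judgement to explain why there is no such committee. It routes serious unexpected events to the data manager and on to the Steering Committee within 24 hours.
- **Dissemination plans {31a}** says that the hospital's PD ward physicians will receive the findings and "directions on implementation if they wish to utilize it with their patients".

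**The concern.** The stated reason does not bear on the thing being tested. fNIRS is a measuring device used in both PD arms, so its safety says nothing about a difference between them. The audio premise concerns volume at hospital assessments, not listening during home training. What differs between the arms is a daily repetitive movement task in people with a movement disorder, and the harms section does not discuss it.

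This is not a detail left to a fuller document. The article has a harms section, and that section takes an explicit position and gives a reason for it. If the position is followed, non-serious complaints will not be recorded systematically in either PD arm. Strain, pain or fatigue would be examples; they are illustrations of this review, not of the document.

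At stake is what the trial can tell the physicians who receive its directions for use. They would have efficacy and disease-scale results, but no comparative information on how well the exercise is tolerated.

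**Working it through.** The plan gives no figure on this point, so there is none to reproduce. The check compares the relevant sections and then works out the exposure.

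**1. Does any other section plan to collect non-serious events?**

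- Outcomes {12}: no harm or tolerability outcome is listed.
- Strategies to improve adherence {11c}: intervention videos are scored for adherence and accuracy only.
- Criteria for discontinuing {11b}: being unable to continue home training is foreseen as a reason to stop, but harm is not named as a cause.
- Missing data and non-adherence {20c}: missing and non-adherent data are dropped from the analysis. Someone who stops because of discomfort could leave the analysis with no harm recorded.
- Informed consent {26a}: the form describes foreseeable risks and discomfort, but no section plans to record whether they occur.
- Trial steering committee {5d}, data monitoring {21a} and harms {22}: these cover serious events that are unexpected or unforeseen, and no others.

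No section does so.

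**2. Is the serious-event route consistent?**

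- Data monitoring {21a}: on its natural reading, the Steering Committee hears within 24 h.
- Harms {22}: 24 h to the Trial Manager, then a further 48 h to the Steering Committee, so up to 24 + 48 = 72 h.
- Harms {22} also says that no reporting plan applies and then sets one out.

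**3. Exposure in the intervention arm** (inputs from Intervention description {11a} and Sample size {14})

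- Sessions per participant: 8 weeks × 7 days = 56.
- Tapping time: 56 × (2 × 10 min) = 1,120 min; 1,120 / 60 ≈ 18.7 h.
- Sessions in the arm with full adherence: 70 × 56 = 3,920. With 63 participants: 63 × 56 = 3,528.

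**4. What asking could show (illustrative)**

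Assume 63 completers: 70 × (1 − 0.10) = 63. Sample size {14} does not make clear whether 70 is before or after attrition, so 70 completers is the other end of the range. With zero events among n participants, the 95% upper bound on the event rate is about 3/n (rule of three), or exactly 1 − 0.05^(1/n).

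| Completers | Rule of three | Exact |
|---|---|---|
| 63 | 3/63 = 4.8% | 4.6% |
| 70 | 3/70 = 4.3% | 4.2% |

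Without systematic collection, no such bound can be stated for non-serious events.

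**The case against.** The strongest case for the plan has several parts.

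**Serious events are covered.** A reader might infer from the quoted sentence that the trial cannot detect or report harms at all. The documents do not support that. The next sentences of the harms section set a timed route for unforeseen serious events, and two other sections assign responsibility for it. This stands, and it limits the point to non-serious harms.

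**The committees judged the intervention itself low risk.** This also stands as a fact, and data monitoring {21a} states it without mentioning fNIRS. In Outcomes {12}, however, the judgement is presented as following from fNIRS safety. In {21a} it justifies having no monitoring committee, which is a different matter from recording events. Low expected risk supports light collection, not none.

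**Home training is watched.** It would be wrong to call the sessions unsupervised. Participants film each session, caregivers are asked to monitor, a research assistant reviews the videos and phone support is available. But the videos are scored for adherence and accuracy, not for adverse events.

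**Worsening of the disease is measured.** UPDRS, MoCA and the n-back task are taken at baseline and at weeks 4, 8 and 12 in both PD arms. This stands. The gap is in events outside those scales.

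**No harm rate or future safety claim is documented.** This is correct. Nothing in the article shows that the tapping causes harm, and it does not promise a statement that no harms occurred. The 4.8% is a hypothetical bound, and the exposure figures are for scale only.

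The trial is exploratory, and neither the randomised comparison nor any listed primary outcome is affected. That bears on how much weight the point carries, not on whether it is correct.

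**Conclusion.** The concern holds in a limited form. The article rules out an adverse event reporting plan for reasons that concern the measuring equipment and the assessment audio, not the 8 weeks of daily home tapping. Serious unexpected events have a reporting route, although the waiver contradicts it and its timelines differ between sections (24 h against up to 72 h to the Steering Committee). Non-serious harms are not planned to be collected or compared between the PD arms, so the trial could not report on tolerability after about 18.7 h of tapping per fully adherent participant.

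The conclusion rests on the article's explicit text. The exposure figures assume that every session is completed. The zero-event bound of about 4.8% assumes 63 completers (4.3% with 70) and is illustrative. The change is worth making because it is cheap and the results are meant for clinical use; the validity of the efficacy comparison does not depend on it.

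**What to change.** 1. Ask one open adverse event question, in the same words, at the existing week 4, 8 and 12 visits in both PD arms. Record onset and outcome, and report counts by arm.
2. Restate the rationale in Provisions for post-trial care {30}, Outcomes {12} and Adverse event reporting and harms {22} so that it refers to the tapping intervention. The committees' low-risk judgement can be cited there as a judgement on the intervention.
3. Reconcile the waiver in {22} with the serious-event procedure that follows it, and reconcile the Steering Committee timeline in {22} with the one in data monitoring {21a}. Which timeline applies is for the sponsor and the committees to settle.

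The cost is one form item, a few minutes at each of three visits already planned, one table of counts and some edits to the text. No visit is added, and treatment and the primary analysis do not change.
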